### Data management

All patient data collected during this clinical trial will be maintained as an electronic case report form (eCRF) in a web-based central platform (eVelos System: Velos, Inc., Fremont, CA) at the CRCC. The management team at the CRCC will review the eCRFs, and queries will be sent out to each investigative site regularly. Data monitoring will also be conducted by way of site visits. The data will be managed and analyzed according to the study protocol.

### Safety assessment

When a total of 50 patients are enrolled and the allocated surgeries are completed, safety of the experimental intervention or laparoscopic stomach-preserving surgery with SBD, will be evaluated in terms of the occurrence of postoperative complications. Subsequently, the IDMC will evaluate the results of the safety analysis and provide a recommendation as to whether the trial should proceed.

Any serious adverse events (SAEs) will be documented in the medical records, as well as, in the eCRF and reported to the IRB by the responsible investigator, in accordance with the local regulations. SAE is defined as a postoperative complication of Grade III or above based on the Clavien-Dindo classification system [21], or readmission within one month after the surgery.

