#### The following individuals were excluded from the study

i.Patients with a lesion satisfying the absolute indications of endoscopic resection (<2 cm, mucosal lesion, differentiated type)ii.Patients who are not indicated for surgical treatment due to serious cardiovascular or pulmonary diseaseiii.Pregnant womeniv.Patients with a past history of drug-related anaphylactic reaction, prior upper abdominal surgery (except for laparoscopic cholecystectomy) or radiation therapyv.Patients diagnosed with other malignancy within 5 years

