### Intervention

#### Experimental group

##### Procedures for SBD

A detailed description of the SBD procedure is provided in our preceding report on the quality control study for the SENORITA trial [19]. Briefly, a mixture of indocyanine green (IGC; Diagnogreen®, Daiichi-Sankyo Co., Ltd., Japan; 2 mL, 5 mg) and radiolabeled human serum albumin (Tc99m-HSA; 2 mL, 0.1 mCi/mL) is used as a tracer to detect the SNs. The tracer is uniformly prepared at the reference center and delivered to the participating institutions. A 4-mL volume of the dual tracer is injected into the submucosal layer in 4 quadrants of the primary tumor via an intraoperative endoscopic approach. After 15 min of the endoscopic tracer injection, the sentinel basins containing SNs (green or hot) are carefully dissected and retrieved from the surgical field.

The harvested sentinel basins are then dissected to isolate lymph nodes, whilst in the operating room. All the isolated lymph nodes from the sentinel basins, defined as sentinel basin nodes (SBN), are classified into hot nodes (HN: radioactive nodes), green nodes (GN: stained nodes), both hot and green nodes (HGN), and basin nodes (BN: nodes within the sentinel basins, but neither hot nor green), labeled with the respective lymph node station numbers, and sent to the pathologist for intraoperative frozen section evaluation.

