#### Secondary outcomes

The secondary endpoints of this trial include postoperative morbidity and mortality, QOL, and 5-year DFS and overall survival. Postoperative morbidity and mortality occurring within 30 days after the surgery will be reported and graded according to the modified Clavien-Dindo severity classification [21].

QOL will be assessed by the validated Korean version of the European Organization for Research and Treatment of Cancer (EORTC) questionnaires. The enrolled patients will be requested to fill out the core questionnaire (QLQ-C30) and the gastric cancer-specific module (QLQ-STO22) annually up to 3 years after the surgery [22, 23].

The trial will be assessed primarily based on the 3-year DFS. In the likelihood that the number of target events is insufficient for statistical analysis after the 3 years of follow-up, the 5-year DFS and overall survival will be reported as an alternative at the end of the study.

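### The SAE definition leaves out serious intraoperative events that resolve during surgery, including reactions to a tracer given only in the experimental arm

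*Protocol article*

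**What the plan says.** The Safety assessment section gives the SAE definition in two parts. The first is: "SAE is defined as a postoperative complication of Grade III or above" on the Clavien-Dindo system. The second is: "or readmission within one month after the surgery". Events meeting the definition go into the medical records and the eCRF, and are "reported to the IRB by the responsible investigator, in accordance with the local regulations".

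The same section sets a safety review once 50 patients have been enrolled and operated on. The safety of the experimental procedure "will be evaluated in terms of the occurrence of postoperative complications", and the IDMC then advises whether the trial should go on.

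The morbidity endpoint under Secondary outcomes has the same scope: "Postoperative morbidity and mortality occurring within 30 days after the surgery will be reported and graded".

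Under Procedures for SBD, within the experimental group, a mixture of indocyanine green and radiolabelled human serum albumin "is used as a tracer to detect the SNs". It is given by endoscopy during the operation: "A 4-mL volume of the dual tracer is injected into the submucosal layer in 4 quadrants of the primary tumor". The Control group section mentions no tracer. Among the exclusion criteria is: "Patients with a past history of drug-related anaphylactic reaction".

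**The concern.** The SAE definition is a stated rule, not a summary that points elsewhere. It has two parts and no general limb for events that are life-threatening, fatal or prolong the hospital stay. Both parts look at what happens after surgery. The exposure that only the experimental arm receives, the tracer, happens during surgery. Followed as written, the rule leaves a serious reaction that is treated and over before the operation ends without an SAE record, and the 50-patient review does not ask for it.

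Two things are at stake. One is a patient-safety signal specific to the new procedure, which the IDMC may not see when it gives its first recommendation. The other is the comparison of SAEs between arms, which would be incomplete for a hazard present in one arm only.

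**Working it through.** No figure in the document needs to be reproduced, because the point is about the scope of a definition. The check is to take each kind of serious intraoperative event and ask which stated measure would record it, reading each measure by its wording.

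| Event | SAE: postoperative Grade III+ | SAE: readmission within one month | 50-patient review | 30-day morbidity and mortality | DFS event |
|---|---|---|---|---|---|
| Tracer reaction, resolves during surgery | no | no | no | no | no |
| Other serious intraoperative event, either arm, resolves during surgery | no | no | no | no | no |
| Intraoperative event with postoperative consequences below Grade III | no | no, unless readmitted | yes | yes | no |
| Intraoperative event with Grade III or higher postoperative consequences | yes | not needed | yes | yes | no, unless fatal |
| Intraoperative event leading to readmission | depends on grade | yes | if recorded as a complication | if within 30 days and recorded as a complication | no, unless fatal |
| Death during the operation | not clearly | no | not clearly | not clearly | yes, as death from other cause (Primary outcome) |

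The first two rows are recorded by none of the measures. The last row is recorded through the primary endpoint but not clearly through the SAE route.

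**Size.** The document gives no rate of intraoperative events in either arm, so any size rests on an assumption. Take a serious tracer reaction rate p of 0.1 to 1 % (assumed), 290 experimental patients (Sample size calculation), all of them injected, and a share f of reactions that resolve during surgery (unknown, between 0 and 1).

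- Expected reactions: 290 × p = 290 × 0.001 = 0.29, up to 290 × 0.01 = 2.9.
- Expected reactions missed: 290 × p × f. This reaches 0.29 to 2.9 only if f = 1, and is smaller otherwise.
- At the 50-patient review, with about half allocated to each arm (25 patients): 25 × 0.001 = 0.025, up to 25 × 0.01 = 0.25 expected reactions.

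**What a zero count would mean.** If no tracer-related SAE were reported in 290 patients, the one-sided 95 % upper bound would be 1 − 0.05^(1/290) = 0.0103, or 1.03 %. Under the present definition that bound covers reactions with Grade III or higher postoperative consequences or with readmission. It does not cover reactions that resolved in theatre.

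**The case against.** The strongest reply is that the gap is narrow. A reaction whose effects persist after surgery at Grade III or above is an SAE, and so is one that leads to readmission. A fatal reaction is a DFS event, counts towards the 12 events that trigger the interim analysis, and so comes before the IDMC. The Study design section also gives the IDMC a general monitoring role. All of this stands, and it limits the point to events that resolve during surgery and to the unclear SAE status of an intraoperative death.

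A second reply is that this is a journal article, and that adverse-event forms and the content of the safety report belong in the full protocol. This holds for the forms. It does not hold for the SAE definition and the scope of the 50-patient review, which the article itself states. Reporting under local regulations may bring some of these events to the IRB by another route. By its wording, however, that phrase governs how SAEs are reported and does not widen what an SAE is.

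Several stronger readings are tempting and are not supported:

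- **The safety comparison is biased in favour of the experimental arm.** The definition applies to both arms and also omits intraoperative events of the control gastrectomy that resolve during surgery. Only the tracer component runs one way. Without rates, the net direction is unknown.
- **A zero SAE count says nothing about tracer risk.** It still bounds reactions with serious postoperative consequences or readmission.
- **The anaphylaxis exclusion shows that tracer reactions were foreseen.** The criterion refers to drugs in general and does not name the tracer. If it was aimed at the tracer, it would also lower the risk.

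**Conclusion.** The point holds in a limited form. As written, serious intraoperative events that resolve during surgery are outside the SAE definition, the 50-patient review and the 30-day morbidity endpoint, in both arms. Tracer reactions are the one component of this omission that is unequal between arms by design. A death during the operation is a DFS event but not clearly an SAE.

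The likely number of missed tracer reactions is small: at most about 0.3 to 2.9 among 290 patients, if the assumed rate of 0.1 to 1 % holds and every reaction resolves in theatre. The primary endpoint, the sample size and the non-inferiority decision are not affected. The wording should still be corrected, because the omitted events are serious, the exposure is specific to the procedure under test, and the correction is cheap.

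**What to change.** In the Safety assessment section, extend the SAE definition in both arms to serious events (fatal, life-threatening or prolonging the hospital stay) from the start of the procedure, and name tracer reactions explicitly. Keep the two existing parts. State that a death during the operation is an SAE. Tabulate intraoperative SAEs by arm, and add them to the 50-patient review that goes to the IDMC.

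The cost is a change of wording in the protocol and the eCRF and a few more reports. The experimental arm's SAE count may become slightly less favourable, and the control arm's count may rise as well.

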### Interim analysis

When the number of events reaches 12 (50 % of the expected number of events), an interim analysis will be performed to identify any evidence of definite inferiority of the experimental intervention. The IDMC will subsequently evaluate whether the trial should be continued or terminated based on the results of the interim analysis.

### Statistical analysis

Non-inferiority of the experimental study arm will be claimed if the lower confidence limit of 3-year DFS in the experimental study group exceeds 92 %. For survival analyses, the Cox proportional hazards model will be used. Kaplan-Meier curves will be used for survival curve estimation. Categorical variables will be analyzed by the Pearson’s *χ*^2^ test or Fisher’s exact test and continuous variables will be evaluated by the Student’s t-test or appropriate non-parametric method as required. The level of statistical significance will be set at 5 %.

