**Methods/Design:**

This trial is an investigator-initiated, open-label, multicenter randomized controlled phase III trial with a non-inferiority design. Patients diagnosed with a single lesion of clinical stage T1N0M0 gastric adenocarcinoma, with a diameter of 3 cm or less are eligible for the present study. A total of 580 patients (290 per group) will be randomized to either laparoscopic stomach-preserving surgery with SBD or standard surgery. The primary end-point is 3-year disease-free survival (DFS) and the secondary endpoints include postoperative morbidity and mortality, quality of life, 5-year DFS, and overall survival. Qualified investigators who completed the prior quality control study are exclusively allowed to participate in this phase III clinical trial.

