### Outcome measurement

#### Primary outcome

The primary endpoint of the SENORITA trial is 3-year DFS of laparoscopic stomach-preserving surgery with SBD compared to that of conventional laparoscopic gastrectomy with lymphadenectomy in gastric cancer patients diagnosed as clinical stage T1N0M0. To assess DFS in this trial, the criteria for the event is as follows: recurrence of the primary tumor at resection margins, metachronous cancer development at the remnant stomach, histologically proven or radiologically apparent recurrence in the peritoneal cavity including intraabdominal lymph nodes, distant metastasis, newly developed malignancy in other organs, and other cause of death.

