### Sample size calculation

The primary endpoint of this clinical trial is 3-year DFS of patients with gastric cancer of clinical stage T1N0M0. The required sample size was calculated based on a non-inferiority design assuming 97 % of patients achieve 3-year DFS following standard surgery. The margin of non-inferiority was 5 % and type 1 error was set at 0.05 with 80 % statistical power. As such, a sample size of 261 in each group with 24 target events is required. After considering a potential dropout rate of 10 % over the follow-up period, the final sample size is estimated as 290 patients in each study group (580 patients in total).

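### Non-inferiority is decided from the experimental arm alone against a fixed 92 % limit, so the randomised control arm cannot affect the primary conclusion

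*Protocol article*

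**What the plan says.** The protocol article describes a comparison throughout. The abstract calls the study an "open-label, multicenter randomized controlled phase III trial with a non-inferiority design". The Primary outcome section defines the endpoint as "3-year DFS of laparoscopic stomach-preserving surgery with SBD compared to that of conventional laparoscopic gastrectomy with lymphadenectomy". The Sample size calculation section proceeds by "assuming 97 % of patients achieve 3-year DFS following standard surgery" and adds: "The margin of non-inferiority was 5 % and type 1 error was set at 0.05 with 80 % statistical power". It arrives at 261 patients per group with 24 events, and 290 per group after dropout.

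The Statistical analysis section gives the only criterion for the primary claim: non-inferiority will be "claimed if the lower confidence limit of 3-year DFS in the experimental study group exceeds 92" %. The Cox model and Kaplan-Meier curves are named next, for survival analyses in general. Neither is tied to the non-inferiority decision, and no other section states a between-arm criterion.

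**The concern.** The 92 % threshold is 97 % minus 5 points, so a planning assumption stands in for the control arm. Once the data are in, the 290 control patients cannot change the primary conclusion, whatever their outcome.

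The substitution is harmless only if true control DFS is 97 %. If control does better, a procedure that is worse by the full margin can be declared non-inferior. If control does worse, a procedure just as good as standard surgery tends to fail. The endpoint makes such a departure plausible in either direction, because the DFS event also includes new cancers in other organs and deaths from other causes, in patients aged up to 79. A concurrent randomised control exists to measure that background rate. As written, the trial reports a test against a fixed benchmark and labels it a randomised non-inferiority result.

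**Working it through.** **Inputs.** From Sample size calculation: control DFS 97 %, margin 5 points, type 1 error 0.05, power 80 %, 261 per group, 24 events, 10 % dropout. From Statistical analysis: claim if the experimental lower limit exceeds 92 %. Assumed here: complete 3-year follow-up and, to show the range, true control DFS between 94 % and 99 %.

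**1. The stated size comes from two-arm formulas.** The hazard ratio at the margin is ln(0.92)/ln(0.97) = 2.737. With one-sided 0.05 and 80 % power, (1.645 + 0.842)² = 6.183.
- Schoenfeld events: 4 × 6.183 / (ln 2.737)² = 24.4, against 24 stated.
- Freedman events: 6.183 × (3.737/1.737)² = 28.6. Patients per group: 28.6 / (0.03 + 0.08) = 260.1, so 261, as stated.
- Dropout: 261 / 0.90 = 290, as stated.

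A one-arm test of 92 % against 97 % would need about 140 patients (one-sided 0.05) or 183 (two-sided 0.05) and no control group. The size is that of a between-arm comparison; the decision rule is not.

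**2. What the rule requires.** The Wald lower limit is p − 1.96 × √(p(1 − p)/261).
- 13 events: p = 0.9502, limit 0.9238, claim.
- 14 events: p = 0.9464, limit 0.9190, no claim.

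The interval method and its sidedness are not stated, and the cut-off depends on them: 12 events with an exact or log-log two-sided 95 % limit, 13 with Wald two-sided 95 % or exact one-sided 5 %, 14 with Wald one-sided 5 %.

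**3. Probability of a claim.** For the fixed rule this is the binomial P(X ≤ cut-off) with n = 261. For the two-arm rule (upper limit of control minus experimental below 5 points) it is an exact enumeration over both arms. Each two-arm range runs from the Newcombe to the Wald interval. All entries are percentages.

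| True control / experimental DFS | Fixed, cut-off 12 | Fixed, cut-off 13 | Fixed, cut-off 14 | Two-arm, two-sided 95 % | Two-arm, one-sided 5 % |
|---|---|---|---|---|---|
| 97 / 92 (false claim) | 2.2 | 3.9 | 6.7 | 2.4–3.3 | 4.8–6.0 |
| 98 / 93 (false claim) | 7.5 | 12.0 | 18.1 | 2.4–3.6 | 4.8–6.3 |
| 99 / 94 (false claim) | 20.8 | 29.6 | 39.5 | 2.1–4.1 | 4.8–6.9 |
| 97 / 97 (correct claim) | 94.7 | 97.3 | 98.7 | 87.1–91.3 | 93.1–95.0 |
| 95 / 95 (correct claim) | 45.5 | 56.7 | 67.3 | 71.1–75.4 | 81.2–84.0 |
| 94 / 94 (correct claim) | 20.8 | 29.6 | 39.5 | 64.4–68.3 | 75.7–78.2 |

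The fixed rule's false-claim rate climbs steeply as control DFS rises above 97 %. The two-arm rule's rate stays close to nominal.

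**4. Two possible data sets, two-sided 95 % limits.**
- 13 experimental against 3 control events (95.0 % against 98.9 %): declared non-inferior by the Wald limit, yet the upper limit for the difference is 6.8 points (Wald) or 7.3 (Newcombe), beyond the margin.
- 15 against 16 events (94.3 % against 93.9 %): rejected under every cut-off above, yet the upper limit is 3.7 points (Wald) or 3.8 (Newcombe), inside the margin.

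**The case against.** The strongest defence is that the sentence is shorthand for the margin, 97 − 5 = 92, and that the comparative endpoint and the Cox model show a between-arm analysis was intended. That may be so. But the printed sentence is a complete rule, not a gap left for the analysis plan, and a plan that followed it would carry the error forward.

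Four narrower points stand in part.
- The harm depends on control DFS departing from 97 %. At 97 % the fixed rule is close to its nominal error. The other control rates are illustrations, not predictions.
- Part of the 12 % and 30 % comes from the Wald interval, which already gives 3.9 % against a nominal 2.5 % at control 97 %. With an exact or log-log two-sided 95 % limit the figures are 7.5 % and 21 %. The direction does not change.
- A two-arm rule also loses power as DFS falls, so the fixed rule causes only part of the drop from 97 % to 57 % or 30 %.
- At 97 % in both arms the two-arm rule is less likely to succeed than the fixed one, because it carries the control arm's sampling error. That is a real cost.

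The absence of a cited source for 97 % is not held against the article, which may leave it to the full protocol.

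**Conclusion.** The concern holds. The decision rule contradicts the comparative endpoint, the randomised design and the two-arm sample size. With a two-sided 95 % limit and the experimental arm worse by the full margin, false claims reach 7 to 12 % at a true control DFS of 98 % and 21 to 30 % at 99 %. A two-arm rule stays at about 2 to 4 %. With equal arms at 95 % or 94 %, the fixed rule succeeds in 45 to 57 % or 21 to 30 % of trials, against 71 to 75 % or 64 to 68 %. These figures assume 261 evaluable patients per arm, complete follow-up and the illustrative control rates. The structural fault does not depend on them. Because this sentence alone settles the primary conclusion, it must be corrected.

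**What to change.** Replace the sentence in Statistical analysis with:

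> Non-inferiority will be claimed if the upper confidence limit for the difference in Kaplan-Meier 3-year DFS (control minus experimental) is below 5 percentage points.

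State the confidence level and whether it is one- or two-sided. One-sided 0.05 is what reproduces the sample size. Preferably name an interval that behaves well near 97 %, such as a Newcombe or score type or one built on log-log limits, since the method moves the boundary by an event or more. The experimental arm's limit against 92 % can be kept as a descriptive result.

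The cost is one sentence and no extra patients. With 261 per arm and 97 % in both, power is 87 to 91 % with a two-sided 95 % limit, or 93 to 95 % with a one-sided 5 % limit, above the planned 80 %. Against the fixed rule with a two-sided 95 % Wald limit (97.3 %), the chance of success at those rates falls by about 6 to 10 points at the same confidence level.

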## Methods/Design

### Study design

The SENORITA trial is an investigator-initiated, open-labeled, parallel-assigned, multicenter randomized controlled phase III trial. It is schematically described in Fig. 1. This study will involve 7 medical institutions (National Cancer Center, Gyeongsang National University Hospital, Ajou University Hospital, Dongnam Institute of Radiological and Medical Science, Yonsei University Severance Hospital, Soonchunhyang University Bucheon Hospital, and Chonnam National University Hwasun Hospital), which have been qualified to participate in this phase III trial following completion of the prior quality control study (NCT01544413) [18, 19].

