### Randomization & allocation

The web-based clinical trial management system (eVelos System; Velos, Inc., Fremont, CA: http://eresearch.ncc.re.kr/velos/jsp/ereslogin.jsp) at the Clinical Research Coordination Center (CRCC) within the National Cancer Center, Korea, will coordinate the study and handle the data analysis. As soon as written informed consent is obtained from the eligible patient, the patient will be registered in the system and randomly allocated to one of the two surgical groups: laparoscopic SBD with stomach preserving surgery or standard laparoscopic gastrectomy with D1+ or more lymphadenectomy according to the Japanese gastric cancer treatment guidelines [1]. To reduce potential bias and confounding, participants will be further stratified based on the institution where the procedure is performed, depth of tumor invasion (mucosa vs. submucosa), and size (≤2 cm vs. > 2 cm) of the primary tumor. The random block size permutation method was used to generate the initial randomization sequence, and the randomization task will be centrally coordinated by the CRCC.

All registered patients will undergo a routine preoperative evaluation, including full laboratory tests, electrocardiogram, chest X-ray, pulmonary function test, and assessment for tumor markers.

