Many investigators have evaluated the applicability of SN navigation surgery in gastric cancer. The results are inconsistent across studies in terms of the accuracy and sensitivity of SN biopsy for detecting nodal metastasis in gastric cancer; however, most of these studies were conducted with a small population at a single center [29]. Nonetheless, a series of recent studies have reported the feasibility of SN navigation surgery in EGC patients [17, 30–35]. Therefore, we herein propose a multicenter randomized clinical trial primarily to elucidate the oncologic safety of SBD with stomach-preserving surgery compared to the standard laparoscopic gastrectomy with lymphadenectomy.

The most challenging aspect of designing a randomized controlled trial involving surgical procedures is that it is difficult to blind the surgeons and patients as to the intervention. Moreover, the ethical concerns with regards to the blinding of patients must also be considered. Therefore, the primary end-point should be a purely objective variable, such as DFS, as in this clinical trial, to minimize potential bias caused by non-blinding. Secondly, the surgical procedure per se is inevitably operator-dependent and can vary among the participating surgeons. As such, it would be challenging to extrapolate the results of a single-institution trial to other centers. A multicenter trial is also associated with biases, such as differences in operative skill and experience, as well as, in perioperative care among participants. The tendency toward such bias would certainly become stronger when the procedure is more complicated and involves investigators from different departments. Therefore, we obtained in-depth advice from experts in the field before the development of this study protocol. We also conducted a quality control study prior to the initiation of this phase III trial to qualify participating institutions [19]. A detailed step-by-step checklist was provided to investigators participating in the previous quality control study. It was recommended that the checklist be completed for at least 10 patients per surgeon to overcome the learning experience. Repetitive discussion during this quality control study allowed participating investigators to achieve consensus and standardize the specific procedures outlined in this subsequent phase III SENORITA trial protocol.

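### The tests named for morbidity and QOL ignore the randomisation strata and the preoperative QOL score; adjusting for them is a free improvement, limited to secondary outcomes

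*Protocol article*

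**What the plan says.** **Randomisation.** Under Randomization & allocation, patients are "stratified based on the institution where the procedure is performed, depth of tumor invasion (mucosa vs. submucosa), and size" (two classes, cut at 2 cm). "This study will involve 7 medical institutions" (Study design), so there are 7 x 2 x 2 = 28 strata. On the method: "The random block size permutation method was used to generate the initial randomization sequence". Block sizes are not given.

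**Centre differences.** The Discussion lists "differences in operative skill and experience, as well as, in perioperative care among participants" among the biases of a multicentre trial.

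**QOL.** Table 2 (Postoperative follow-up schedule) marks QOL preoperatively and at 3, 12, 24 and 36 months.

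**Analysis.** The Statistical analysis section gives Pearson's chi-square or Fisher's exact test for categorical variables; "continuous variables will be evaluated by the Student’s t-test or appropriate non-parametric method as required". For DFS it says "For survival analyses, the Cox proportional hazards model will be used", naming neither strata nor covariates and excluding neither. The non-inferiority criterion is that the "lower confidence limit of 3-year DFS in the experimental study group exceeds 92" per cent.

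**The concern.** The design balances the arms within institution, depth and size, and the authors expect centres to differ. Morbidity and QOL are the outcomes most exposed to surgical skill and perioperative care, and better QOL is the benefit expected from the stomach-preserving operation. The tests named for them leave two sources of variation in the error term.

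- **Strata.** Stratified randomisation removes most of the between-stratum variation from the actual difference between arms. An unstratified standard error still counts that variation, so it is too large when the strata are prognostic.
- **Preoperative QOL score.** This is not a stratification factor, so the t-test standard error is correct in this respect. The comparison is simply less precise than the collected data allow.

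The cost is wider intervals and lower power on secondary outcomes. False-positive claims do not become more likely.

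**Working it through.** **Inputs from the protocol article:** 580 patients randomised; 261 per arm (522) after 10 % dropout; 24 target events; 7 institutions and 28 strata; QOL measured preoperatively.

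**Assumed, because the document gives no figure:** share of outcome variance between institutions (ICC) 0.02, 0.05, 0.10; correlation r between preoperative and later QOL 0.3, 0.5, 0.6; block size 4; unequal centre sizes.

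**1. The plan's own figures.** The hazard ratio implied by 92 % against 97 % is ln(0.92)/ln(0.97) = 2.737. The one-sided 5 %, 80 % power Schoenfeld formula gives 4 x (1.645 + 0.842)² / (ln 2.737)² = 24.4 events, against 24 stated. A one-sided comparison of 97 % with 92 % gives 257 per arm, against 261 stated. Dropout: 261/0.90 = 290, as stated. None of these contains a stratification term, so this point does not alter the sample size.

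**2. Ignoring institution.** The variance that matters is (1 - ICC) of the total, while the unstratified analysis reports the total. Effective patients lost = 580 x ICC; standard error inflation = 1/√(1 - ICC).

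| ICC | Patients lost, of 580 | Standard error too large by |
|---|---|---|
| 0.02 | 11.6, about 12 | 1.0 % |
| 0.05 | 29 | 2.6 % |
| 0.10 | 58 | 5.4 % |

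With the 522 patients left after dropout, the losses are 10, 26 and 52.

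**3. Ignoring the preoperative QOL score.** The variance remaining after adjustment is 1 - r².

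| r | Variance remaining | Variance removed | Interval narrower by 1 - √(1 - r²) |
|---|---|---|---|
| 0.3 | 0.91 | 9 % | 5 % |
| 0.5 | 0.75 | 25 % | 13 % |
| 0.6 | 0.64 | 36 % | 20 % |

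**4. Simulation of a continuous outcome.** 522 patients, 28 strata, blocks of 4, standardised effect 0.245, ICC 0.02-0.10, no depth or size effect, 3,000 runs per setting. The adjusted model contains preoperative score, institution, depth and size.

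| r | t-test power | Adjusted power |
|---|---|---|
| 0 | about 81 % | 81-83 % |
| 0.3 | 81-82 % | 84-87 % |
| 0.5 | 79-81 % | 89-93 % |

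Coverage of the unadjusted nominal 95 % interval was 94.8-96.3 %; adjusted coverage stayed near 95 %. The strata alone are therefore worth up to about 2 points of power here. The larger gain comes from the preoperative score.

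**5. Does the same hold for DFS?** Simulation with 522 patients and 28 strata, with assumed depth, size and centre effects ranging from none to very strong:

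- The standard error of the unadjusted 3-year difference exceeded the true standard deviation by at most about 2 % with equal DFS (0.0148 v 0.0145) and about 4 % with the experimental arm at 92 % (0.0197 v 0.0190). Both needed the strongest effects.
- Coverage of the nominal 90 % interval was 0.895-0.915.
- A Mantel-Haenszel stratified difference had practically the same standard deviation.
- With about 25 events, a Cox score test stratified on all 28 cells carried 2.5-4.5 % less information than the unstratified one (6.28 v 6.44 with no effects; 5.80 v 6.07 with the strongest).

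For DFS there is practically nothing to recover, and full stratification has a cost.

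**The case against.** **This is an efficiency preference, and a SAP may settle it.** The named tests are valid and err on the safe side. That stands, and it is why the point ranks low. But for morbidity and QOL the article does name specific methods, and those methods cannot take a stratum or a covariate. The mismatch is in the text; it is not inferred from silence.

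**A reader might infer that the Cox model is unstratified.** The document does not support this. It leaves the strata and covariates open, and a condensed article commonly leaves them to the full protocol or SAP.

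**A reader might also infer that non-inferiority loses power.** It does not follow. The stated rule compares one arm's lower limit with 92 % and has no treatment contrast to stratify. Adjusting a Cox model for prognostic factors also does not generally narrow the interval of the log hazard ratio.

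**The magnitudes are assumed.** True: the document gives neither the between-institution variance nor the QOL correlation. The upper figure should not be read as 64: 580 x (1/0.90 - 1) = 64 is the number of extra patients an unadjusted analysis would need, whereas the loss is 580 x 0.10 = 58.

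**The preoperative score is not a stratification factor.** Correct. Its gain is a separate argument for the same change to the analysis, and no evidence of a mismatch with the randomisation.

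**The authors already address centre differences.** They do so through the prior quality control study, the checklist and the qualification of institutions. These reduce the differences and make the lower end of the ICC range more plausible. They do not show that the differences are nil.

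**Conclusion.** The point holds for postoperative morbidity and QOL only, as a free improvement of low severity. The named tests are valid but mildly conservative if the strata are prognostic: about 12-58 of 580 patients' worth of interval width at an assumed ICC of 0.02-0.10. For QOL the preoperative score matters more, with a further 9-36 % of variance at assumed correlations of 0.3-0.6. If institutions hardly differ and baseline QOL predicts little, the gain is close to nil. The sample size, the type I error and the stated non-inferiority decision on DFS are unaffected.

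**What to change.** In the Statistical analysis section, or in the SAP if it governs:

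- **Morbidity:** compare the arms with a Mantel-Haenszel test stratified by institution.
- **QOL:** use a model containing the preoperative score, institution, depth and size.
- **Sensitivity:** keep the chi-square or Fisher test and the t-test or non-parametric test as unadjusted sensitivity analyses.
- **DFS:** state which factors, if any, enter the comparative Cox model, and do not stratify it on all 28 cells with about 24 events.

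The cost is a few sentences and a little analysis work. No new data or patients are needed, since the strata are recorded at randomisation and the preoperative QOL assessment is already scheduled.
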